**Quality control**

TCM doctors participating in this trial are required to be attending physician or higher in title with relatively abundant clinical experience and have enough time and energy to be dedicated to this clinical research. All the investigators including TCM doctors, drug administrators and outcome assessors have trained of the Standing Operating Procedure (SOP) in order to get a thorough understanding of the protocol and the principal parameters of the study. An auditor has arranged to monitor the process of study, supervise the study progression and check the reliability of records. Moreover, we have set up an adverse event monitoring system. The type, starting and ending time, clinical manifestation, treatment process, and prognosis of adverse effects will be well-recorded. The relationship of adverse effects with drugs will be assessed according to the 5 grades formulated by the monitor center of the Ministry of health of China, including certainly related, probably related, probably unrelated, certainly unrelated and unable to judge. The certainly related or probably related adverse effects will be recognized as drug related adverse effects.

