**Sample size**

The sample size has been calculated according to our preliminary results [[[8]](#endnote-9)]. The mean reduction of UAER in the control group was 30.19, and that in TSF group was 81.67. The ratio of patients between the treatment group and the placebo group is designed as 2:1. The sample size has been estimated to be 56 in the control group, and 112 in the treatment group. Assuming a dropout rate of 15%, 90% power to detect and a 0.05 two-side level of significance, the sample size of DKD patients has been estimated to be 192.

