**Blindness**

Double-blinding method is adopted in this study. As the package, color, smell and taste of the placebo is the same as TSF, so researchers and participants won’t know the kind of medicine and group allocation. It was not allowed for the drug administrator to neither contact with investigators, nor exchange information with patients. They are trained how to illustrate the usage and dose of this formula for the patients but not to convey any treatment information to participants.

The outcome assessment will be conducted by independent researchers who don’t know the group allocation of patients.

Figure 1: The flowchart of the trial:

Screening for type 2 diabetic kidney disease with microalbuminuia /marcoalbuminuia individuals

Sign consent

Inclusion criteria achieved?

Run-in period (2 weeks)

NO

Excluded

Primary outcome:

UAER & 24h urinary protein

Secondary outcome (1):

Scr，BUN， eGFR

Blood lipid

Secondary outcome (2):

TCM syndrome & quality of life

Completed the 24-wk administration

**TSF group**：

TSF+ACEI/ARB

**Placebo group**： Placebo + ACEI/ARB

Visits and clinical measurements, medication

at 4,8,12,16,20,24 weeks

YES

Randomization

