**Adverse events**

Adverse events (AE) refer to adverse medical events occur after treatment with a drug, which do not necessarily have a causal relationship with the treatment. Serious adverse events (SAE) include death, hospitalization or prolonged length of hospitalization, disability and congenital malformations. We have established the adverse event monitoring system and defined the three-grade criteria of adverse events: the first level as it could be endured or only mild discomfort with no affection of daily life; the second level as it causes discomfort and affects daily life; the third level as it causes handicap to self-care ability.

**Possible adverse events due to TSF:** TSF contains the herbal medicine rhubarb, which may lead to the following adverse events to participants: 1) Diarrhea and secondary constipation: Loose stools and diarrhea are the most common adverse reactions of rhubarb. Severe cases may have symptoms of dehydration, such as sunken eyes, dry lips and fatigue. Tannic acid in rhubarb has anti-diarrhea action. Taking rhubarb for a long time can cause stress reaction reduction of intestinal nerve cell, leading to rhubarb dependent constipation. 2) Melanosis coli: Herbal medicine with strong cathartic actions usually contains anthraquinone derivatives, which may cause colon melanosis coli. Diagnosis of melanosis coli is mainly based on microscopic examination and biopsy specimens. Taking rhubarb for a long-term or with a high dosage can increase the secretion of intestinal mucus glands, make intestinal epithelial cells produce more histocompatibility complex, and increase macrophage activity and chemotaxis. Then the macrophage phagocytosis is strengthened, causing colon melanosis coli. 3) Other adverse events: A few cases reported that application of rhubarb might cause elevated ALT and serum creatinine, which were mainly due to excessive intake without instruction of a physician.

**Possible adverse events due to ACEIs/ARBs:** The main side effects of ACEIs and ARBs are dry cough, rise of serum potassium and rise of serum creatinine.

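### The drug-related adverse-event count leaves out events graded unable to judge, so in either arm it may be too low by the number of such events

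*Protocol*

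**What the plan says.** In the Protocol, section Quality control, causality is rated on a five-level scale: "The relationship of adverse effects with drugs will be assessed according to the 5 grades". The grades are "certainly related, probably related, probably unrelated, certainly unrelated and unable to judge". The next sentence sets the dividing line: "The certainly related or probably related adverse effects will be recognized as drug related adverse effects". No other sentence says how the fifth grade is handled.

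Three other places bear on the point:

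- **Adverse events** defines an adverse event without a causal link, as events "which do not necessarily have a causal relationship with the treatment". Table 1 collects adverse events at every visit from week 0 to week 24.
- **Blindness** says that "researchers and participants won’t know the kind of medicine and group allocation", so one rule is applied to both arms without knowledge of allocation.
- **Adverse events** lists a rise in serum creatinine as a possible effect of rhubarb, a component of TSF. For the background treatment that every participant receives it says: "The main side effects of ACEIs and ARBs are dry cough, rise of serum potassium and rise of serum creatinine".

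**The concern.** The five grades hold three kinds of information: judged related (two grades), judged unrelated (two grades) and not judged (one grade). The rule reduces them to two classes and leaves the third kind on the same side as the unrelated events. The Protocol does not expressly call these events unrelated, but a table built from the sentence as written would omit them from the drug-related line. Incomplete information would then lower that line.

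This is a rule that the Protocol states, not a detail left open for a statistical analysis plan. A plan that followed the sentence would carry the same exclusion.

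Safety is half of the single stated trial objective. Events that are hard to attribute are also foreseeable here. A creatinine rise appears in the expected effects of both a TSF component and the ACEI/ARB background treatment, so a careful blinded rater may be unable to say whether the study medication caused it.

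**Working it through.** The Protocol gives no adverse-event count, rate or share graded unable to judge, so there is no stated figure to reproduce. The check is a logical one, with illustrations on assumed values.

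**1. What the rule omits.** Let R be the number of events graded certainly or probably related, and U the number graded unable to judge.

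- Count under the rule: R
- Count of all events not judged unrelated: R + U
- Difference: (R + U) − R = U

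Assume R = 20 and let U run from 0 to 20. The rule gives 20 throughout, and the inclusive count runs from 20 to 40. The shortfall is 0 at one end and 20 of 40 events at the other. This holds for events. If patients are counted, the shortfall is at most the number of patients with a fifth-grade event, because a patient who also has a related event is counted already.

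**2. Comparison with the true number.** Let q be the share of U that is truly drug related and f the share of R that is not. Leave aside related events misgraded as unrelated.

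- True number: T = R(1 − f) + Uq
- Rule minus truth: R − T = Rf − Uq
- Inclusive count minus truth: (R + U) − T = Rf + U(1 − q), which is never negative

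With assumed R = 20, U = 10, q = 0.5:

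| f | T | Rule − T | Inclusive − T |
| --- | --- | --- | --- |
| 0 | 20 + 5 = 25 | 20 − 25 = −5 | 30 − 25 = +5 |
| 0.25 | 15 + 5 = 20 | 20 − 20 = 0 | 30 − 20 = +10 |
| 0.5 | 10 + 5 = 15 | 20 − 15 = +5 | 30 − 15 = +15 |

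The rule's count can lie on either side of the truth. Under the stated simplification the inclusive count can only be too high, which is why it is the conservative one.

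**3. Effect on the comparison of arms.** The section Sample size states: "The ratio of patients between the treatment group and the placebo group is designed as 2:1". With 192 patients this gives 192 × 2/3 = 128 on TSF and 192 × 1/3 = 64 on placebo. Assume 24 and 6 patients with an event not judged unrelated, and a share s of them unable to judge, equal in both arms.

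- Including the fifth grade: 24/128 = 18.8% and 6/64 = 9.4%; difference 9.4 points, ratio 2.0
- Under the rule, s = 25%: 18/128 = 14.1% and 4.5/64 = 7.0%; difference 7.0 points, ratio 2.0

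In general the difference is multiplied by (1 − s) and the ratio does not change. For s from 10% to 30% the TSF rate falls by 0.10 × 18.8 = 1.9 to 0.30 × 18.8 = 5.6 points, and the placebo rate by 0.10 × 9.4 = 0.9 to 0.30 × 9.4 = 2.8 points. All event counts and shares in this step are assumed.

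**The case against.** The strongest reply is that nothing is lost. Adverse events are collected regardless of causality, with type, timing, manifestation, treatment and prognosis recorded. The section Safety assessment rests on laboratory tests and ECG with no causality filter. The sentence in Quality control only defines a label, and how the fifth grade is tabulated could be settled in a statistical analysis plan that is not shown. Much of this stands: the data will exist, an all-event comparison by arm remains possible, and its absence from the Protocol is no finding. It does not remove the point, because the label itself is fixed in the Protocol and excludes unassessed events from any drug-related line built on it.

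A reader might infer more than the documents support:

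- **That the TSF drug-related rate is understated.** No rate is given, U may be zero, and an unassessable event is no evidence of a relation either. Step 2 shows that the sign of the error against the truth is open.
- **That the rule favours TSF.** It applies to both arms under blinding, and it rates the relationship with drugs in general. With equal shares removed, the ratio is unchanged and only the absolute difference shrinks.
- **That unassessable events are likely because the Background criticises earlier evidence.** That text concerns the size, controls and monitoring of earlier trials, not causality grading.
- **That this is the only adverse-event count defined.** The sentence defines a category. The adverse-event definition and the three severity levels do not depend on causality.

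It can also fairly be said that counting every unassessed event as related is only one convention and may overstate the rate in both arms. Showing the count with and without the grade meets this.

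**Conclusion.** The point holds as a minor one. As written, the rule leaves events graded unable to judge out of the drug-related count, alongside the two unrelated grades. The count in either arm may therefore be too low. Relative to a count that includes the grade, it is lower by exactly the number of such events.

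That number cannot be obtained from the Protocol and may be zero. The illustrated shortfalls (0 to 20 events; 1.9 to 5.6 points on TSF and 0.9 to 2.8 points on placebo) rest wholly on assumed counts and show only how the rule works. The documents do not establish that the count is too low against the true number of drug-caused events, that the effect is specific to TSF, or that the comparison between arms is biased as a ratio.

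**What to change.** Replace the last sentence of Quality control with wording to this effect:

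> Adverse events not judged unrelated (certainly related, probably related, or unable to judge) will form the drug-related count. Events graded unable to judge will also be shown on a separate line for each arm, so that the count can be read with and without them. Both will be presented beside all adverse events by arm, regardless of causality.

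The cost is a changed sentence and one more table line. No new data are needed, since the grade is already recorded. The downside is that the drug-related rate may look slightly less favourable in either arm and may include some events that no drug caused. The separate line lets a reader take them out again.
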